#### **4.3 Laboratory Tests**

All participants will have blood samples (**App D**) taken at baseline, end of the Total Diet Replacement phase, and on completion of study for:

**Routine Biochemistry** - Liver Function tests, urea and electrolytes, cholesterol, triglycerides, high density lipoproteins: HbA1c and glucose. Additional analyses will be carried out to explore changes in insulin, hsCRP, Ferritin, Urate and creatinine. Additional tests may be added, if indicated by new information, using the existing samples, to add information about safety or pathophysiology of T2D in people of South Asian origin.

II blood samples will be processed by, Central Glasgow laboratory (BHF GCRC, University of Glasgow).

GP's will be asked to repeat participants HbA1c at the end of the Total Diet Replacement phase and end of the study, as part of routine NHS care, to reassess diabetic status and establish their on-going treatment needs. These samples will be processed in an NHS laboratory.

During the period of restrictions due to COVID-19

- Participants will be asked to attend Glasgow Clinical Research Facility on completion of TDR and at the end of FR to have blood samples for HbA1c taken and blood pressure checked. These measurements will be taken by CRF nursing staff. Should the NHS CRF facilities and staff at GRI not be available, the necessary follow-up checks will be carried out by [name] (PI) at the Human Nutrition Metabolic Room in the New Lister Building.
- Blood samples will be processed by NHS GG&C laboratories and results accessed via Portal by the research dietitian. GPs will be informed of the results and the need for recommencement of medications discussed as required.

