### **Food Reintroduction (FR) phase (weeks 12-18):**

A stepped transition to food based Weight Maintenance, replacing TDR with meals which contain 30% of energy from fat. Some further modest weight loss will occur.

**Week 13:** step down to 400kcal/d LELD + 1 low-fat meal/day (c. 360-400 kcal) + 2 servings of fruit, 200mls skimmed milk and free vegetables. Total intake will be 1000kcal/day.

**Week 15:** step down to 200kcal/d LELD + 2 low-fat meals/day (c. 720-800 kcal) + 2 servings of fruit, 200mls skimmed milk and free vegetables. Total intake will be 1200kcal/day.

**Week 17:** 3 low-fat meals per day (c.1080-1200 kcal) + 2 servings of fruit, 200mls skimmed milk and free vegetables. Total intake will be 1400kcal/day.

**Week 18:** 3 low-fat meals per day (c.1080-1200 kcal) + 2 servings of fruit, 200mls skimmed milk and free vegetables. Advice to increase by 200kcal per day until weight loss maintenance achieved. Option to join BEYOND Study.

During this phase participants will attend for review appointments every 2 weeks. To allow flexibility for patients whose confidence varies, the food introduction phase will be permitted to be varied between the protocol-defined limits of 2-8 weeks before switching to full food-based weight maintenance. Reasons for moving to weight loss maintenance without completing food reintroduction will be recorded. If patients are unable to attend appointments, they will be offered telephone consultation as necessary but with encouragement to attend clinics as the preferred method of contact.

During the period of restrictions due to COVID-19

- Participants will not be seen in person for study appointments. Appointments/consultations will be carried out, by, the study research dietitian, by telephone/text/e-mail, whichever is preferred by the participant.

On completion of the feasibility study, at the end of FR we will provide participants with advice, and written information, on maintaining weight loss, which will include goal setting, self-monitoring, physical activity, relapse prevention if weight tends to rise again, and education on food labelling and eating out. Participants will then be returned to the care of their GP, who will be informed

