## **5. ASSESSMENT OF SAFETY**

Given the nature of the intervention there is very low likelihood of safety concerns. Patients allocated to the intervention will be closely monitored throughout the study with review appointments 2 weekly during the TDR and Food Reintroduction phases. At each appointment blood pressure and postural symptoms will be monitored and antihypertensive therapy reintroduced if necessary according to clinical guidelines.

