## **Appendix E: Protocol for management of blood pressure**

### ***Background***

Antihypertensive and diuretic drugs will be stopped on the day the total diet replacement is commenced.

This is a safety measure, because blood pressure is likely to fall on the diet.

This protocol lays out the standard approach to be followed to allow clear description of the research findings. Individual clinical decisions may be necessary for a person's best interest.

The level of 140mmHg is chosen to allow safe decisions during the weight loss period. After the Food Reintroduction period follow usual guidelines for management of hypertension.

To simplify decision making, systolic pressure only is used as a guide to therapy even though both systolic and diastolic are relevant to long term benefit.

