### ***Protocol***

#### ***When antihypertensive drugs are stopped, re-emphasise the importance of avoiding sodium (salt)***

1. In the first 2 weeks after stopping antihypertensives and diuretics:  
If systolic BP over 165 mmHg on repeated measurement - restart one drug, as below.
2. Thereafter, if systolic BP is >140 mmHg - restart one drug as below.
3. Increase dose weekly to achieve target.
4. If systolic BP remains >140mmHg on the first drug - add a second drug, as below.
5. Increase dose weekly to achieve target.
6. Repeat as necessary with third, fourth or more drugs (increasing each to maximum dose).

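### The COVID-19 provisions give no source for blood-pressure readings between the end-of-TDR and end-of-FR checks, although antihypertensives are still withdrawn and their restart depends on those readings

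*Protocol*

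**What the plan says.** **Withdrawal.** Appendix E states: "Antihypertensive and diuretic drugs will be stopped on the day the total diet replacement is commenced". Section 4 (TDR phase) and section 4.1 (Appt 1) give the same instruction. None of the three has a COVID-19 exception.

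**Monitoring.** Section 5 states: "At each appointment blood pressure and postural symptoms will be monitored and antihypertensive therapy reintroduced if necessary according to clinical guidelines".

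**Restart rule.** For the first 2 weeks after stopping, Appendix E says: "If systolic BP over 165 mmHg on repeated measurement - restart one drug, as below". After that: "Thereafter, if systolic BP is >140 mmHg - restart one drug as below". Once a drug is restarted: "Increase dose weekly to achieve target".

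**COVID-19 provisions.** The clause at the end of the Food Reintroduction text in section 4 says: "Participants will not be seen in person for study appointments". Contact is instead "by telephone/text/e-mail, whichever is preferred by the participant". Section 4.3 has participants attend the Clinical Research Facility "on completion of TDR and at the end of FR to have blood samples for HbA1c taken and blood pressure checked". It names a back-up location if that facility is unavailable, and has GPs told of the results so that restarting medication can be discussed.

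**The concern.** The restart rule acts on a measured systolic pressure. The COVID-19 text takes away the visits at which that pressure would be measured, keeps two of them, and does not say where the other readings come from. The drug withdrawal that makes the readings necessary is left unchanged.

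A participant whose antihypertensives were stopped and who is then followed remotely could therefore be above 165 mmHg early on, or above 140 mmHg later, for weeks without the protocol's own trigger being applied. Raised blood pressure may cause no symptoms, so a telephone conversation may not reveal it. What is at stake is the safety of those participants.

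**Working it through.** The plan states no figure on this point, so the check is a count of scheduled readings set against the COVID-19 text.

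**Inputs**
- Blood pressure after baseline (Appendix A): weeks 1, 2, 4, 6, 8, 10, 12, 13, 15, 17 and 19, which is 11 readings.
- Readings named in the COVID-19 text (section 4.3): end of TDR (week 12) and end of FR (week 19), which is 2 readings.
- Drug stop: week 0 if TDR starts at once (section 4, Appendix E), or week 0+1 (section 4.1, Appt 1). In the second case the Appt 1 reading coincides with the stop and is not a reading after withdrawal.
- TDR length: 12 weeks, extendable to 20 (section 4).

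**Reading A: the remote clause covers all study appointments**

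| | Stop at week 0 | Stop at Appt 1 (week 1) |
|---|---|---|
| Scheduled readings after withdrawal | 11 | 11 − 1 = 10 |
| Remaining | 2 | 2 |
| Lost | 11 − 2 = 9 (9/11 = 82%) | 10 − 2 = 8 (8/10 = 80%) |
| Scheduled in the first 2 weeks after stopping | 2 (weeks 1, 2) | 1 (week 2) |
| Of these, remaining | 0 | 0 |
| Time to first reading, 12-week TDR | 12 − 0 = 12 weeks | 12 − 1 = 11 weeks |
| Time to first reading, 20-week TDR | 20 − 0 = 20 weeks | 20 − 1 = 19 weeks |

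On this reading the 165 mmHg threshold has no scheduled measurement to act on.

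**Reading B: the remote clause covers FR only**

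The TDR readings are kept. Of the four FR readings (weeks 13, 15, 17, 19), three are lost and week 19 is kept. The gap is 19 − 12 = 7 weeks.

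**Which reading?** The clause sits under the Food Reintroduction heading, which favours B. Its wording refers to study appointments in general, and section 4.3 treats the end of TDR as a special attendance, which would be unnecessary if TDR visits stayed in person. That favours A. The text does not settle it.

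**Who is affected?** Participants on antihypertensives or diuretics who were already in TDR or FR when restrictions applied, or controls who crossed over to the intervention during them. The full gap under A falls on those who start TDR under restrictions. Someone already part-way through TDR would have had some clinic readings. The protocol gives neither the number treated remotely nor the number on these drugs. The note on optional tests in section 4 speaks of recruitment recommencing, so it appears to have paused, which limits new TDR starts.

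**The case against.** The strongest reply is that section 4.3 adds two attendances without saying that they are the only blood-pressure checks. Section 5 is not suspended, and a remote appointment does not rule out a reading taken at home or by the GP. Standard care continues in both arms, Appendix E allows individual clinical decisions, adverse events are asked about at each visit, and section 5 sends findings that may pose a risk to the patient and GP.

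This stands in part. A reader might infer that the monitoring and restart rules cannot be followed at all during restrictions, but the documents do not say that. They leave the source of the readings unstated. The safeguards listed do not fill the gap, because each needs a reading or a symptom to act on. The discussion with the GP about restarting medication in section 4.3 follows the results of the two attendances.

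Three other strong inferences also go too far:
- That the 11-to-12-week gap is certain. It depends on reading A.
- That many of the 25 participants are exposed. Recruitment appears to have paused, and only those on these drugs count.
- That the study's results are distorted. Restart of antihypertensives is not among the outcomes in section 4.2, and nothing here touches weight or remission.

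**Conclusion.** The concern holds as a safety gap in the COVID-19 provisions. Drugs are withdrawn, the restart rule needs blood pressure, and between the two listed checks the protocol names no source for it.

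The size depends on two ambiguities in the text. If all appointments are remote, 80% to 82% of the readings after withdrawal have no stated source, including every reading in the first 2 weeks. If only FR is remote, three readings and about 7 weeks are affected. The counts assume the Appendix A schedule; FR itself may vary from 2 to 8 weeks. The number of people affected is unknown and probably small. This is more than a detail left open, because following the COVID-19 text as written removes the trigger for a stated safety rule, and the remedy is cheap.

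**What to change.** Add to the COVID-19 provisions in sections 4 and 4.3, in words such as these:

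*Participants whose antihypertensive or diuretic drugs are withdrawn will be loaned a home blood-pressure monitor and will report readings at every remote appointment, including within the first 2 weeks after withdrawal. The Appendix E thresholds apply to these readings, and the source of each reading will be recorded. If home readings cannot be obtained, a GP or Clinical Research Facility check will be arranged on the same schedule, or the start of TDR will be deferred.*

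The same amendment should say whether the remote clause covers TDR as well as FR.

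Starting TDR with antihypertensives continued and no readings would not be a safe fallback. Appendix E presents withdrawal as a safety measure because pressure is expected to fall on the diet.

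The cost is a few sentences of protocol text and a small equipment outlay, at most one monitor for each affected participant. Where home readings work, no extra visits are needed. The drawback is that self-measured readings are less standardised than those taken by study staff, which is why the source should be recorded.

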## **5. ASSESSMENT OF SAFETY**

Given the nature of the intervention there is very low likelihood of safety concerns. Patients allocated to the intervention will be closely monitored throughout the study with review appointments 2 weekly during the TDR and Food Reintroduction phases. At each appointment blood pressure and postural symptoms will be monitored and antihypertensive therapy reintroduced if necessary according to clinical guidelines.

### **Appendix E**

Patients will be given clear guidance on detecting deteriorating glycaemia to permit hypoglycaemic agents to be reintroduced if necessary. If capillary blood glucose is  $\geq 20\text{mmol/l}$  at any appointment we will ask the participants GP check the participants HbA1c. Results will be discussed with the participants GP to allow decisions on changes to medications to be made.

Any observations/results which may pose a risk to health will be discussed with the patient and their GP.

## **6. STATISTICS AND DATA ANALYSIS**

The main objective of the study is to investigate if Counterweight Plus is acceptable to individuals of South Asian origins. This study is not powered to achieve a primary outcome, rather to investigate if it is possible to recruit, retain and achieve remission from diabetes in the South Asian population. Data will be collected on paper-based forms and entered into a secure SPSS file for analysis. Drug intolerance, diet intolerance or poor-compliance will be recorded. Trial documentation and data will be retained for at least 5 years.

## **6.1 Sample size**

We aim to recruit 25 participants to the study. This figure has been chosen as this will give us enough information to assess the feasibility and acceptability of the programme to this population. We anticipate a failure to complete rate of about 25% (this may be greater at specific timepoints due to the COVID-19 pandemic). With 20 participants in a randomized comparison, the study can estimate the change in weight with a margin of error of 2.8kg assuming a standard deviation weight change over 3 months of 6kg. e.g., for an average observed weight change of 8kg (SD 6) we can estimate with 95% confidence that in the population the true weight change would lie between 5.1 and 10.7kg.

The proportion achieving remission in the combined intervention and delayed intervention groups (n=20) will be compared to the proportion achieving diabetes remission in the external DIADEM-1 trial control group (Taheri et al, Lancet Diabetes and Endocrinol, 2020) (12%; 95%CI 5%, 21%). Therefore assuming 12% remission in a usual care group (based on DIADEM), using a one sample proportion test, with 20 participants there will be 83% power to detect a significant difference if 30% of participants (n=6) or more achieve remission.

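### Section 6.1: 25 recruits with about 25% non-completion give 18–19 completers, but the weight margin and the remission power both use 20, and the protocol does not explain the 20

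*Protocol*

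**What the plan says.** All the inputs are in protocol section 6.1. The target is "We aim to recruit 25 participants to the study". The loss assumption follows: "We anticipate a failure to complete rate of about 25% (this may be greater at specific timepoints due to the COVID-19 pandemic".

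Two numerical claims then rest on 20 participants:

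- Precision: "With 20 participants in a randomized comparison, the study can estimate the change in weight with a margin of error of 2.8kg". The SD behind this figure is taken as 6 kg at three months.
- Remission: "The proportion achieving remission in the combined intervention and delayed intervention groups (n=20") is set against an external control rate, "assuming 12% remission in a usual care group (based on DIADEM), using a one sample proportion test", and the section concludes that "with 20 participants there will be 83% power to detect a significant difference if 30% of participants (n=6) or more achieve remission".

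The section does not say how 20 was obtained from 25.

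Section 3.5 also bears on this. Routine-care data continue to be collected on people who withdraw, for up to 12 months unless they refuse, and the analysis is to use the best available routine weights and the end-of-study diabetes status of those who stop the programme.

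**The concern.** A sample-size paragraph that states a recruitment target and a loss rate is normally read as leading to the number used in the next sentence. Here it does not: the stated loss leaves about one participant fewer than the 20 used. The mismatch is on the favourable side, and the same sentence warns that losses may be higher.

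At stake is whether the stated precision and power belong to the group the study expects to have. The study exists to inform a larger trial, and programme retention is one of its main outcomes (section 4.2). An attrition assumption that does not match its own denominator could be carried forward into that planning.

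**Working it through.** **Inputs (all from section 6.1).** Recruits 25; failure to complete about 25%; n = 20 for both claims; SD of weight change 6 kg; 95% confidence; null remission rate p0 = 0.12; alternative p1 = 0.30, equated with 6 of 20.

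**Step 1: the number of completers.**

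- 25 × (1 − 0.25) = 18.75, so 18 or 19.
- 20 of 25 is 80% completion, a loss of 20%.
- 20 completers at 25% loss would need 20 / 0.75 = 26.7, so 27 recruits.
- 20 × 1.25 = 25. Adding 25% to 20, instead of dividing 20 by 0.75, would produce exactly the printed target. The protocol does not say whether this was done.
- If each of 25 recruits completed independently with probability 0.75, the chance of 20 or more completers would be 38%.

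**Step 2: the weight margin.** Half-width = t(0.975, n − 1) × 6 / √n.

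- n = 20: 2.81 kg. This reproduces the printed 2.8 kg.
- n = 19: 2.89 kg.
- n = 18: 2.98 kg.

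With 1.96 in place of t, the values are 2.63, 2.70 and 2.77 kg, so on that formula 2.8 kg is still met at n = 18. The reproduced figure is a one-group margin for within-person change. Although the text speaks of a randomised comparison, a 10 versus 10 difference would have a half-width of about 5.6 kg.

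**Step 3: the remission power, first at the plan's own n = 20.**

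- Normal approximation, one-sided 5%: Φ[(p1 − p0 − 1.645 √(p0(1 − p0)/n)) / √(p1(1 − p1)/n)]. At n = 20 this is Φ[(0.18 − 1.645 × 0.0727) / 0.1025] = Φ(0.590) = 72.2%.
- Exact binomial, success defined as six or more remissions: P(X ≥ 6) is 0.026 under 12% and 58.4% under 30%.
- Other normal versions at the 5% level (different variance choices, arcsine, continuity correction) run from 54% to 80% one-sided and from 42% to 70% two-sided.
- At one-sided 10%, the normal figure is 80.2% and the exact figure is 76.2%.

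None of these gives 83%. For the rule of at least 6 of 20, an 83% chance of success needs a true remission rate near 38%.

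**Step 4: the part due to dropout.**

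| n | Normal, one-sided 5% | Exact, ≥6 remissions | Attained one-sided alpha, ≥6 | Attained one-sided alpha, ≥5 |
|---|---|---|---|---|
| 20 | 72.2% | 58.4% | 0.026 | 0.083 |
| 19 | 70.7% | 52.6% | 0.020 | 0.069 |
| 18 | 69.1% | 46.6% | 0.015 | 0.056 |

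The loss is 1.5 points (n = 19) to 3.1 points (n = 18) on the normal approximation, and 5.8 to 11.8 points on the exact rule. The exact loss is larger because six remissions are still required at each n; five do not reach one-sided 5%.

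The exact result also depends on sidedness. At one-sided 2.5%, the exact test needs seven remissions at n = 20 (alpha 0.0067, power 39.2%) but six at n = 19 and n = 18. The 6-to-12-point loss therefore belongs to the six-or-more rule that the section implies, tested at one-sided 5%.

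**The case against.** The strongest reply is section 3.5. Failing to complete is not the same as being absent from the analysis. Routine weights and diabetes status of discontinuers are to be used, and section 4.3 has GPs repeat HbA1c at the end of total diet replacement and at the end of the study. Section 6.1 never calls its 20 participants completers. The analysable number could therefore lie anywhere from 18–19 up to 25, and 20 is within that range. This stands. It rules out saying that 20 is impossible, and it rules out insisting that the loss be restated as 20%.

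It does not explain the 20, however. Section 6.1 gives the loss rate immediately before using 20 and does not refer to section 3.5. Routine data also need not supply a result at the end of total diet replacement, which is when the synopsis places the primary endpoint. A control participant lost during the three-month wait would have no post-intervention result to contribute to the combined group.

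Three further replies stand as limits on the size of the point:

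- The rate is given as approximate and the gap is 1.25 participants: losing 5 of 25 is 20%, losing 6 is 24%.
- The precision claim hardly changes.
- Section 6 says the study is not powered for a primary outcome, and section 6.1 justifies 25 mainly as enough to judge feasibility and acceptability.

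A reader might infer that dropout is why neither printed figure is achieved. The documents do not support that. The margin is almost unchanged, and the 83% already fails with all 20 participants.

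**Conclusion.** The inconsistency is real but small. Target, loss rate and n do not agree within section 6.1, the disagreement is in the optimistic direction, and neither possible explanation (a 20% loss, or partial use of discontinuers' data) is stated.

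If only completers are analysed, the margin widens by about 0.1 to 0.2 kg. Power for 12% against 30% falls by about 1.5 to 3 points (normal approximation, one-sided 5%) or 6 to 12 points (exact, six or more remissions). If discontinuers are analysed under section 3.5, the loss may be smaller or nil.

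The larger shortfall, from the printed 83% to 72.2% (normal) or 58.4% (exact) at n = 20, is a separate error in the power figure and should not be attributed to attrition.

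These sizes assume the section's SD of 6 kg and its 12% and 30% rates. The section names only a one-sample proportion test, so the exact and one-sided versions are assumptions here. Section 6.2 refers to a statistical analysis plan that was not available and may settle the test.

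**What to change.** Change section 6.1 only. Make the three numbers consistent in one of these ways:

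- use about 19 participants, with 18 as the lower case because losses may be higher; or
- keep 20 and state a 20% loss; or
- keep 20 and state that it includes discontinuers analysed under section 3.5.

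Then restate both figures for the chosen n. Describe the margin as one-group, within-person change: 2.8 kg at n = 20, 2.9 kg at 19, 3.0 kg at 18. Give the power with the test and its sidedness named, for example exact one-sided 5%, six or more remissions: 58% at n = 20, 53% at n = 19, 47% at n = 18. If 6 remissions is kept as the illustrative count, its percentage must follow the n: 6 of 20 is 30%, 6 of 19 is 32%, 6 of 18 is 33%.

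The cost is a wording change, with no extra enrolment and no change in conduct. The stated power becomes less favourable, mainly because the 83% is corrected and only slightly because of dropout.

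### The 2.8 kg margin of error in Section 6.1 is the precision of one group's mean weight change, not of a randomised comparison of 20 people

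*Protocol*

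**What the plan says.** Section 6.1 of the protocol gives the only quantitative justification for the weight outcome: "With 20 participants in a randomized comparison, the study can estimate the change in weight with a margin of error of 2.8kg". The SD it takes for the 3-month change is 6 kg. As an illustration it supposes an observed mean change of 8 kg with that SD and concludes that "we can estimate with 95% confidence that in the population the true weight change would lie between 5.1 and 10.7kg".

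The surrounding text fixes what the 20 can be. Section 3.1 recruits 25 patients in total and randomises them to control or intervention. Section 3 and the synopsis (Methodology) keep the control arm on usual care for 3 months, after which it receives the programme too. The second paragraph of Section 6.1 again uses n = 20, this time explicitly for the immediate and delayed intervention groups combined. No allocation ratio is stated anywhere in the protocol.

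**The concern.** A randomised comparison estimates a difference between two arms. Its precision depends on the number in each arm and on the variability in both. A mean change in one group of 20 is a different quantity, with a much smaller standard error than a difference between two groups that together make up 20. The sentence names the first and gives the precision of the second.

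This matters because the synopsis (Rationale) sets out to assess weight change against routine care, and the results are to inform a larger randomised trial. A reader who takes the sentence at its word would expect an 8 kg difference between arms to carry an interval of about ±2.8 kg, when the design gives roughly one and a half to two times that. The same reader could also take an uncontrolled before-after change for an effect measured against control.

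**Working it through.** **Inputs**
- Number analysed: 20 (Section 6.1), a total over both arms because 25 are recruited in all (Section 3.1).
- SD of 3-month weight change: 6 kg (Section 6.1).
- Confidence level: 95%, two-sided (Section 6.1).
- Allocation: not stated; 1:1 is assumed.
- SD in controls: not stated separately; taken as 6 kg and then varied from 0 to 6 kg.

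**1. Reproducing the plan's figure.** One-sample half-width = t(0.975, n−1) × SD/√n.
- n = 20: 2.093 × 6/√20 = 2.093 × 1.342 = **2.81 kg**. This is the stated 2.8 kg. The normal quantile would give 2.63 kg.
- n = 19: 2.89 kg.

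**2. The example interval.** 8 ± 2.81 = 5.19 to 10.81, that is 5.2 to 10.8 kg. The printed limits, 5.1 and 10.7, have half-width (10.7 − 5.1)/2 = 2.8 but midpoint (5.1 + 10.7)/2 = 7.9, not 8.

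**3. The difference between arms.** Half-width = t(0.975, n₁+n₂−2) × √(SD₁²/n₁ + SD₂²/n₂).

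| Split | SD in both arms | Half-width |
|---|---|---|
| 10 v 10 | 6 kg | 2.101 × 6 × √(2/10) = **5.64 kg** (normal: 5.26) |
| 9 v 10 | 6 kg | 5.82 kg |
| 12 v 13 (no loss) | 6 kg | 4.97 kg |
| 20 v 20 (if 20 meant per arm) | 6 kg | 3.84 kg |

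None gives 2.8 kg, and 20 per arm is impossible with 25 recruited. For a total of 20 with equal SDs, 10 v 10 gives the smallest half-width, because 1/n₁ + 1/n₂ is smallest when the arms are equal. An unequal split would therefore widen it.

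**4. A smaller SD in controls** (10 v 10, intervention SD 6 kg, 18 df): 2.101 × √(36/10 + s²/10).

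| Control SD, s | Half-width |
|---|---|
| 0 kg | 3.99 kg |
| 2 kg | 4.20 kg |
| 3 kg | 4.46 kg |
| 4 kg | 4.79 kg |
| 6 kg | 5.64 kg |

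Even controls with no variation at all leave the margin at about 4.0 kg.

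**5. What 2.8 kg on the difference would need.** With SD 6 kg in both arms, about 37 per arm (36 by the normal formula), or 74 in total against 25 recruited.

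**6. The example as a difference.** 8 ± 5.64 gives about 2.4 to 13.6 kg under 10 v 10 and SD 6 kg in both arms.

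**The case against.** The best defence is that the calculation was always about a single mean. The sentence speaks of a change in weight, the SD is that of a change, the example is one mean change, and no control value or treatment difference appears. The next paragraph of Section 6.1 uses the same n = 20 for the pooled intervention groups. On that reading one phrase is misplaced and the number is sound. This largely stands, and it limits the point to a wrong label. It does not remove the point, since the pooled before-after change is not a randomised comparison.

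Four stronger readings are tempting, and the documents do not support them.
- *The protocol claims to know the effect against control to ±2.8 kg.* A reader might infer this from the label, but the text never states a difference between arms.
- *The margin is exactly double.* That needs 1:1 allocation and an SD of 6 kg in controls. The protocol states neither, and Section 4 asks controls not to try to lose weight, so their SD may well be smaller.
- *Planning of the larger trial is compromised.* The synopsis (Methodology) treats controls later in order to learn the distribution of weight changes, and it is this information that feeds the future power calculation. For that use, the single-group precision is the relevant one.
- *Dropout makes n = 20 wrong.* A 25% loss from 25 leaves 18.75, but the plan says about 25%, and n = 19 moves the margin only from 2.8 to 2.9 kg. Section 3.5 also uses routine-care weights for people who discontinue, so leaving the programme is not the same as a missing weight.

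**Conclusion.** Wrong as written, and of moderate weight. The 2.8 kg is correct for the mean within-person change in one group of 20 with SD 6 kg, and it is attached to a comparison for which it cannot hold. For a difference between arms with 20 people in total, the half-width is about 5.6 kg under 1:1 allocation and SD 6 kg in both arms, and about 4.0 to 5.6 kg as the control SD runs from 0 to 6 kg. Both assumptions are the reviewer's, but the gap from 2.8 kg remains across that whole range. The 0.1 kg shift in the example interval is a genuine slip without consequence.

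The point does not invalidate the sample size. Section 6 and the synopsis (Statistical Analysis) declare a feasibility study that is not powered, and Section 6.1 chooses 25 to assess feasibility and acceptability.

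**What to change.** In Section 6.1:
- Remove the reference to a randomised comparison. Describe ±2.8 kg (±2.9 kg if 19 are analysed) as the 95% margin of error for the mean weight change over the programme in the pooled immediate and delayed intervention participants, with SD 6 kg.
- Correct the example interval to 5.2 to 10.8 kg.
- If a precision for the randomised 3-month difference is wanted as well, give it separately as about ±5.6 kg (4.0 to 5.6 kg depending on the control SD). State that this assumes 10 per arm. This addition is optional; the first two changes are enough to remove the error.

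The cost is a sentence or two of rewording. Recruitment, endpoints, analysis and patient care do not change. The only downside is that any stated precision for the controlled comparison becomes less favourable.
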